#### Secondary Analyses

The one-sided non-inferiority 90% confidence interval approach (as described above) to evaluate noninferiority using the difference in change from baseline mean scores for the continuous clinical measures; GDS [51], BDI [52], BAI [66], SF-36 [67]; for the Telepsychology and Same-Room conditions will be used. The magnitude of the difference in the means (effect sizes), as estimated by the confidence intervals will provide useful clinical information and will allow a clinical judgment relative to the clinical non-inferiority of the two modes of delivery. The hypothesis testing approach to evaluating noninferiority, as described by Dunnett and Gent [56] and Farrington and Manning [57], will also be used.

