### Study Instruments and Data Collection Schedule

Self-report measures will be used to evaluate clinical outcome at baseline, mid-treatment (4-weeks), post-treatment (8-weeks), 3-months, and 12-month follow-up. Process outcomes will be evaluated at 4-weeks, 8-weeks, 3-months, and 12-months. Resource Utilization surveys will be administered at baseline, and then 3 and 12 month follow-up. Endpoint psychiatric interviews (ie, Structured Clinical Interview for DSM-IV, [SCID]) [50]; will be administered at baseline and 12-months by raters blind to subject condition. Structured interviews will be audiotaped, and 20% will be rated by an independent to ensure interrater reliability. The complete assessment takes about 120 minutes. Study assessments will be administered by either the Research Coordinator. Assessment clinicians will not deliver treatment. Their training will include instruction, assigned readings, modeling, role-playing, and feedback.

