For the ITT sample (n_1 _= n_2 _= 100/treatment group) we will be able to estimate the individual (main effects) end of treatment means for each of the continuous clinical and process measures with a precision of ± 0.2 standard deviations. For the primary outcome measure Δ_Δ1 _= Δ_(Post)T_- Δ_(Post)S_, which measures the difference in change from baseline (pre to immediate post treatment) for the continuous outcome domain measures for the telepsychology condition compared to change from baseline for the standard (same-room) condition, we will be able to estimate with a precision of ± 0.3 standard deviation units using 95% confidence intervals for the difference in two means (Δ_(Post)T_, Δ_(Post)S_), where the appropriate standard deviation is the pooled standard deviation for comparing change from baseline for the telepsychology condition versus the standard condition.

Assuming that 20% of subjects will drop out of the ITT sample (n_1 _= n_2 _= 80, assuming equal treatment distribution of dropouts), we will be able to estimate for the completer sample the individual end of treatment means for each of the measures with a precision of ± 0.2 standard deviations, and the difference in change from baseline (pre to immediate post treatment) for the outcome domain measures with a precision of ± 0.3 standard deviation units.

Both the standard deviation and the distribution of costs are presently unknown for the type of patients who will be enrolled in Telepsychology. Thus, it is difficult to obtain a meaningful estimate of the power to detect a difference in CE from any arbitrary value. We propose to determine costs and apply to our economic model after the completion of the study, and then use the bootstrap technique to obtain a 90% Confidence Interval (CI) around the estimated costs. The bootstrap technique is appropriate because, as noted, the distribution of costs for these types of patients is presently unknown.

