In addition to comparing unadjusted % responders between the modes of delivery conditions, it also is of interest to compare % responders, adjusted for putative confounding variables. Possible covariables to be considered for inclusion in these analyses include initial disease severity as measured by baseline GDS or BDI score, use of psychiatric medication, number of other co-morbid conditions, and relevant others as identified though the preliminary descriptive analyses. Two approaches will be used to evaluate non-inferiority of adjusted % responders for the two delivery conditions. The method of Gart and Nam [65] and Nam [59], which involves calculation of a non-inferiority test statistic within strata of potential confounding variables, formulates a score test for a null hypothesis of a common specified clinically relevant non-zero difference in % responders between two treatments for multiple 2 × 2 tables. Because the above procedure may be limited by the number of covariables (number of strata) that can be used, we will carry out a second set of analyses using a multivariable logistic regression model to obtain estimates of adjusted % responding for each treatment delivery condition for a specified set of values for the covariables, and then will apply the methods described above (one-sided confidence intervals and non-inferiority hypothesis testing) to evaluate non-inferiority of the two interventions. The response variable for these analyses is the dichotomous outcome, responder/non-responder to treatment, with missing data from premature exits treated as non-responders. The primary independent variable is treatment condition.

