Exploratory multivariable logistic regression, assuming drop-outs are nonresponders, will be used to determine the set of predictor variables associated with treatment response (dichotomous outcome: treatment responder/nonresponder as described under primary analyses). In additional exploratory analyses, RRM analysis will be used to evaluate the effect of putative confounding or prognostic variables on continuous or binary clinical outcomes following the 8-week treatment course, and the possible effect modification (interaction) of these variables on the relationship between treatment status (delivery mode) and clinical outcome. Interaction between treatment status variables and covariates will be evaluated by inclusion of treatment by covariate interaction terms in the model. In a final set of analyses, we will compare the single end of study measure (change from baseline) for the outcome variable using a multivariable regression approach with treatment status as the primary independent variable, with missing values imputed using the method of Little and Rubin [83]. Analyses will be repeated for each of the clinical measures, both with and without a Bonferroni correction [84] for the multiple outcome variables. In other words, both the unadjusted and Bonferroni-corrected p-values will be obtained to evaluate sensitivity of conclusions to the "multiple comparisons" effect.

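### The secondary non-inferiority intervals for GDS, BDI, BAI and SF-36 use unadjusted change from baseline; adjusting for the baseline already collected would cost nothing and usually narrow them

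*Protocol article*

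**What the plan says.** Under Secondary Analyses, the Protocol article applies "The one-sided non-inferiority 90% confidence interval approach (as described above") to GDS, BDI, BAI and SF-36, in order to "evaluate noninferiority using the difference in change from baseline mean scores for the continuous clinical measures". It names no covariate, time point or margin for these measures, and leaves the size of the difference to clinical judgment.

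Sample Size Determination and Power Analysis describes a similar contrast, from baseline to immediately after treatment: "we will be able to estimate with a precision of ± 0.3 standard deviation units using 95% confidence intervals for the difference in two means". It adds that "the appropriate standard deviation is the pooled standard deviation for comparing change from baseline". That is the yardstick of an unadjusted two-sample comparison of change scores.

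Baseline values exist for all four measures. Table 1 marks each at the baseline visit, and the data collection section says: "Self-report measures will be used to evaluate clinical outcome at baseline, mid-treatment (4-weeks), post-treatment (8-weeks), 3-months, and 12-month follow-up".

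Baseline severity is named as a covariate in one place, Primary Clinical Outcome, where "initial disease severity as measured by baseline GDS or BDI score" is a candidate for the adjusted responder analyses. Under Additional Analyses the plan says "we will compare the single end of study measure (change from baseline) for the outcome variable using a multivariable regression approach", without naming a baseline-score term or linking the result to the non-inferiority interval.

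**The concern.** A change score subtracts the whole baseline value, which fixes its coefficient at 1. The regression slope of follow-up on baseline is usually below 1, so subtraction over-corrects. This has two consequences.

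- **Precision.** The change score carries more variance than a model that estimates the slope, so the confidence limit sits further from the estimate than it needs to.
- **Chance imbalance.** If one arm starts with worse scores by chance, regression to the mean gives it a larger mean change. The difference in change keeps (1 − slope) of that imbalance, and it can favour either arm. The Randomization section states no stratification by baseline severity.

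In a non-inferiority comparison, the conclusion depends on where the confidence limit falls. Avoidable width and a baseline-driven shift therefore both matter, even for secondary measures.

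**Working it through.** **Inputs from the document:** 100 per arm in the intention-to-treat sample and 80 per arm among completers; 95% intervals for the precision statement; one-sided 90% limits for the non-inferiority analyses; stated precision ±0.3 SD of change.

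**Inputs not in the document (assumed):** the baseline-to-follow-up correlation r, taken over 0.3 to 0.8, and the ratio k = follow-up SD / baseline SD, taken as 1 and then as 1.25 and 1.5.

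**Step 1. Reproduce the stated precision.** For an unadjusted difference in mean change, in SD-of-change units, the half-width is z × √(2/n).

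- 100 per arm, 95%: 1.96 × √(2/100) = 0.277
- 80 per arm, 95%: 1.96 × √(2/80) = 0.310
- 100 per arm, one-sided 90%: 1.2816 × √(2/100) = 0.181 from estimate to limit

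The first two match the stated ±0.3, which confirms that the figure describes an unadjusted comparison.

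**Step 2. Effect of baseline adjustment with equal SDs.** Var(change) is proportional to 2(1 − r), and Var(adjusted) to 1 − r². The half-width ratio, adjusted over unadjusted, is √((1 + r)/2). All widths below are in SD-of-change units at 100 per arm.

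| r | Ratio | 95% half-width (unadjusted 0.277) | One-sided 90% distance (unadjusted 0.181) | Unadjusted too wide by | Equivalent n per arm = 100/ratio² |
|---|---|---|---|---|---|
| 0.3 | 0.806 | 0.223 | 0.146 | 24.0% | 154 |
| 0.5 | 0.866 | 0.240 | 0.157 | 15.5% | 133 |
| 0.7 | 0.922 | 0.256 | 0.167 | 8.5% | 118 |
| 0.8 | 0.949 | 0.263 | 0.172 | 5.4% | 111 |

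**Step 3. Unequal SDs.** The ratio becomes √( k²(1 − r²) / (1 + k² − 2rk) ), and the slope is r × k.

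| k | r = 0.3 | r = 0.5 | r = 0.7 |
|---|---|---|---|
| 1.25 | 0.886 | 0.945 | 0.990 |
| 1.5 | 0.933 | 0.982 | 0.999 |

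A ratio of 0.886 means the unadjusted interval is 1/0.886 − 1 ≈ 13% too wide. A ratio of 0.999 means about 0.1%. The gain vanishes as the slope approaches 1; at k = 1.5 and r = 0.7 the slope is 1.05. In large samples the ratio never exceeds 1.

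**Step 4. Baseline imbalance.** The unadjusted estimate is shifted by (1 − slope) × imbalance. With equal SDs and r = 0.5 the slope is 0.5, so an imbalance of 0.2 baseline SD shifts the estimate by 0.5 × 0.2 = 0.10 SD. At r = 0.5 the SD of change is √(2 × 0.5) = 1 baseline SD, so this compares directly with the 0.181 SD from estimate to limit.

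**Step 5. Do other planned analyses remove the point?** The mixed models under Additional Analyses treat week 0 as part of the outcome, and the text does not constrain the arms to equal baseline means. The later regression of change names only treatment. Neither is stated as the source of the non-inferiority limit.

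**The case against.** The strongest reply is that nothing here is invalid. Under randomisation the difference in mean change is unbiased on average, the analyses are secondary, and an imbalance can fall either way. All of that stands.

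A second reply is that adjustment is partly planned. Multivariable regression and mixed models appear under Additional Analyses, baseline GDS or BDI is already a candidate covariate for the responder analyses, and a covariate list is often left to the analysis plan. Secondary Analyses also never calls its comparison unadjusted. This stands in part. However, the precision statement, with its pooled SD of change, points to the unadjusted reading, and adjustment is spelled out only for responders.

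Third, the size depends on two quantities the document does not give. Entry requires major depressive disorder, which may restrict the baseline spread, so a follow-up SD above the baseline SD is plausible. The gain would then be small. This stands and limits the claim.

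Three stronger readings are tempting but not supported:

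- **A power gain.** A reader might take the planned 85% power and infer that it rises to about 92% at r = 0.5 with equal SDs. That 85% belongs to the binary GDS responder endpoint, with its 0.15 margin on response proportions. No margin or power is stated for the continuous measures, so no power gain can be computed for them.
- **One and the same contrast.** The sample size section calls its change contrast a primary outcome measure, and a reader might conclude that a primary analysis is affected. That contrast runs to immediately after treatment and uses 95% intervals. Secondary Analyses gives no time point and uses one-sided 90% limits. The two are similar but not shown to be identical.
- **A wrong precision figure.** The ±0.3 SD reproduces.

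**Conclusion.** The point holds as an avoidable loss of precision in the secondary continuous analyses, together with sensitivity to chance baseline imbalance. It is not an error or a contradiction.

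Assuming equal SDs at baseline and follow-up and correlations of 0.3 to 0.8, the planned interval is about 24% to 5% wider than a baseline-adjusted one. With a follow-up SD 1.25 to 1.5 times the baseline SD, the excess falls to between about 13% and practically nothing over correlations of 0.3 to 0.7. These figures are large-sample results. The responder endpoint and its sample size are unaffected. The change is worth making because it is free, not because the present analysis misleads.

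**What to change.** Under Secondary Analyses, state that for each of GDS, BDI, BAI and SF-36 the one-sided 90% limit comes from an analysis of covariance of the follow-up score (or, equivalently for the treatment coefficient, the change) on delivery mode plus the baseline value of the same measure. Use the same model for the continuous change contrast in Sample Size Determination and Power Analysis. Keep the unadjusted difference in mean change as a sensitivity analysis.

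The ±0.3 SD statement can stay; with adjustment it becomes a conservative figure in large samples.

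The cost is about one sentence of analysis wording and one degree of freedom per model. No additional patients, visits or data are needed.

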### Randomization

The study coordinator will verify all eligibility criteria prior to randomization. The procedure and risks will be explained to the patient and the consent form signed as per standard clinical practice. All subjects will be randomly assigned to one of two groups – Telepsychology (n = 112) and Same Room (n = 112). The randomization sequence will be generated by the senior biostatistician and provided in individual sealed envelopes to the data/statistical analyst who will be responsible for randomization. This information will remain confidential and not shared with the study sites in accordance with the CONSORT guidelines [49]. The study coordinator will call the data/statistical analyst to get subject randomization assignment. Once a randomization assignment is provided, the patient is entered into the study and will be included in the intention to treat analysis (Figure 1).

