### Outcome Measures

#### Clinical Outcome Measures

The primary clinical outcome measure is the proportion (%) of patients who respond to treatment. Treatment Responder status will be determined using each of the dependent measures of depression (ie, Geriatric Depression Scale (GDS) [51]; Beck Depression Inventory (BDI) [52]; and SCID [50]. For the BDI and GDS, treatment responders will be those that demonstrate, at 12-month follow-up, improvement of at least 50% on the total score. For the SCID, treatment responders will be those who are no longer diagnosed with MDD. Dichotomous classifications for the GDS and the BDI will be achieved by defining treatment response as at least a 50% improvement from baseline to post-treatment level (percent change from baseline: [baseline-post]/baseline ≥ 50%). We will report analyses involving each measure of treatment response separately, but will take the a priori position that, in the case where results based on each of these analyses do not converge, overall conclusions regarding treatment response will be based on the two measures that concur. Thus, our indicator of treatment response will be in terms of each measure, as well as in terms of the converging data from at least two different measures.

The primary process outcome is score on the Charleston Psychiatric Outpatient Satisfaction Scale (CPOSS), [53] measured at the end of the 12-month follow-up period. The CPOSS is a 16-item measure with each item having a Likert-type format (total score is sum of the 16 items with range 16–80). Non-inferiority of patient satisfaction at the end of the 12-month follow-up period for the two modes of delivery will be evaluated via the one-sided non-inferiority 90% confidence interval approach to estimate the difference in end of study mean scores on the CPOSS for the Telepsychology and Same-Room conditions. The magnitude of the difference in satisfaction levels, as estimated by the confidence interval will provide useful clinical information and will allow a clinical judgment relative to the clinical non-inferiority of the of the two modes of delivery.

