### Sample Size Determination and Power Analysis

The primary response variable for sample size calculation is the proportion (%) of patients who respond to treatment. Treatment response is defined as at least a 50% improvement from baseline to post-treatment level on the GDS [percent change from baseline: (baseline-post)/baseline ≥ 50%]. Demonstration of non-inferiority among treatments differs from that of establishing superiority. For a non-inferiority trial, the null hypothesis states that two treatments are non-equivalent, that is they differ by at least a clinically relevant amount, Δ. [55-62]. The approach will be formulated in terms of the one-sided non-inferiority problem [55,60,61,63] because it is of interest only to test that the treatment response (% responders) for the Telepsychology mode of delivery is not too low compared to that for the standard Same-Room mode of delivery. Note that, for non-inferiority trials, the consequence of a false positive (ie, claiming the novel therapy [Telepsychology] is worse than the standard therapy [Same-Room] when it is, in fact, non-inferior) is to keep patients on the standard therapy. Therefore, the Type I error rate, α, can be set higher than in traditional superiority trials (eg 0.1–0.2) [64].

We estimate that the % treatment responder for Same-Room delivery (P) is 0.70. We assume that a maximum clinically unimportant difference in response proportion (Δ, the non-inferiority effect size) is 0.15 between Telepsychology and the standard Same-Room service delivery (upper limit of one-sided 90% confidence interval must not be greater than Δ = 0.15 for the conditions to be declared equivalent). Using the tables of Machin and Campbell [64] and assuming Δ = 0.15, one-sided α = 0.10, P = 0.70, and power = 0.85, we estimate that approximately n_1 _= n_2 _= 100 subjects per condition are needed for overall treatment effects comparisons. If we further assume that 10% of subjects will not have at least one post baseline measurement (i.e. will not be included in the ITT sample), then 112 subjects must be randomized to each treatment group to yield the required sample size for the primary intent-to-treat analyses (n_1 _= n_2 _= 100/group).

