### Data Analysis

#### Primary Clinical Outcome

Testing the non-inferiority of the Telepsychology mode of delivery to the standard Same-Room mode in terms of % responders can be carried out through either a confidence interval approach or through a modified hypothesis testing procedure [55-62]. For both approaches, a conclusion that the two modes of delivery are similar in clinical efficacy (non-inferior) requires that the response proportion (% responders) for the standard delivery (Same-Room) cannot exceed by more than Δ the response proportion for the novel delivery (Telepsychology). We assume Δ = 0.15 between the novel delivery and the standard delivery (one-sided non-inferiority). With the confidence interval approach, the upper limit of the one-sided 90% confidence limit for the difference in % responders for the novel delivery (Telepsychology) and the standard delivery (Same-Room) must be 0.15 (Δ) or less to accept the hypothesis of a non-inferior novel treatment. Statistically, this translates into testing a non-zero difference between the treatments, where noninferiority is established by demonstrating that the difference between treatments is less than the maximum clinically unimportant difference in response proportions, Δ[55-57,59,61,62]. The hypothesis testing approach to evaluating equivalency in % responders, with an appropriately adjusted test statistic as described by Dunnett and Gent [56] and Farrington and Manning [57] will also be used.

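### Non-inferiority on CPOSS and on the mean changes in GDS, BDI, BAI and SF-36 is left to clinical judgment of the observed interval, with no margin on any mean scale

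*Protocol article*

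**What the plan says.** All references are to the protocol article.

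- **Margin.** Sample Size Determination and Power Analysis states that the "maximum clinically unimportant difference in response proportion (Δ, the non-inferiority effect size) is 0.15 between Telepsychology" and Same-Room delivery. Primary Clinical Outcome repeats 0.15, again for response proportions. No margin in points or SD units appears anywhere.
- **CPOSS.** Clinical Outcome Measures names the CPOSS total (range 16 to 80) at the end of the 12-month follow-up as the primary process outcome. Its non-inferiority is to be evaluated by the "one-sided non-inferiority 90% confidence interval approach to estimate the difference in end of study mean scores on the CPOSS". The size of the difference shown by the interval is then to support a clinical judgment on non-inferiority.
- **Continuous clinical measures.** Secondary Analyses applies the same interval approach, by reference to the description above it, "using the difference in change from baseline mean scores for the continuous clinical measures": GDS, BDI, BAI and SF-36. The interval "will allow a clinical judgment relative to the clinical non-inferiority of the two modes of delivery".
- **Tests.** Primary Clinical Outcome introduces "The hypothesis testing approach to evaluating equivalency in % responders, with an appropriately adjusted test statistic", citing the Dunnett–Gent and Farrington–Manning procedures. Secondary Analyses names the same two procedures for the four continuous measures. For CPOSS only the interval is named.

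**The concern.** The article itself defines the non-inferiority null as a difference of at least a clinically relevant amount Δ. A non-inferiority conclusion therefore needs a Δ on the scale of the outcome, fixed before the result is known. For the means there is none. The reference back to the primary analysis leads to a limit of 0.15 in proportions, which has no meaning for a difference in questionnaire points.

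The article fills the gap with a judgment made once the interval is visible. If the acceptable loss is settled after the result is seen, the one-sided 10% error rate no longer describes the claim.

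At stake is the primary process claim and the process half of the first research question, which asks about both clinical and process outcomes. For GDS, BDI, BAI and SF-36 there is a further problem: the named test step cannot be carried out as written, because it has neither a margin nor a stated form for means.

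**Working it through.** **Inputs from the article:** "assuming Δ = 0.15, one-sided α = 0.10, P = 0.70, and power = 0.85"; 100 per arm in the ITT sample and 80 per arm among completers; 112 randomized per arm. **Assumed here:** all margins on mean scales, a true difference of zero where power is given, and the correlation r between baseline and follow-up. The SDs of the measures are not given, so results are in units of the SD of the quantity compared: the change score for the clinical measures, the 12-month score for CPOSS.

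**1. The article's own figures reproduce.**
- Responders: n = 2 × 0.70 × 0.30 × (1.2816 + 1.0364)² / 0.15² = 100.3 per arm, against about 100 stated. Then 100 / 0.90 = 111.1, rounded up to 112.
- Precision of the difference in change (95% interval): 1.96 × √(2/100) = 0.277 SD and 1.96 × √(2/80) = 0.310 SD, both stated as ±0.3 SD.

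These figures are sound. What is missing is a decision limit.

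**2. Distance from the estimate to the one-sided 90% limit.**
- 100 per arm: 1.2816 × √(2/100) = 0.181 SD.
- 80 per arm: 1.2816 × √(2/80) = 0.203 SD.

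**3. Largest observed Telepsychology deficit that passes (margin minus that distance).**

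| Assumed margin | 100 per arm | 80 per arm |
|---|---|---|
| 0.3 SD | 0.119 SD | 0.097 SD |
| 0.5 SD | 0.319 SD | 0.297 SD |

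Observed deficits from about 0.12 to 0.32 SD (100 per arm) or 0.10 to 0.30 SD (80 per arm) are decided by which margin is picked.

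**4. Chance of concluding non-inferiority when the true deficit is 0.3 SD, 100 per arm.** Formula: Φ((margin − 0.3)/0.1414 − 1.2816).
- Margin 0.2 SD: 2%.
- Margin 0.3 SD: 10%.
- Margin 0.4 SD: 28%.
- Margin 0.5 SD: 55%.

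**5. Power at zero true difference.** Formula: Φ(margin/√(2/n) − 1.2816).
- Margin 0.3 SD: 80% with 100 per arm, 73% with 80.
- Margin 0.5 SD: 99% and 97%.
- Smallest margin with 85% power: (1.2816 + 1.0364) × √(2/n) = 0.33 SD with 100 per arm, 0.37 SD with 80.

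**6. Baseline adjustment for GDS, BDI, BAI and SF-36.** With equal variances at the two times, the variance under ANCOVA relative to change scores is (1 − r²)/(2(1 − r)) = (1 + r)/2. This is 0.65, 0.75 and 0.85 for r = 0.3, 0.5 and 0.7, so 35%, 25% and 15% less. At r = 0.5 and a 0.3 SD margin with 100 per arm, the standard error falls from 0.1414 to √(0.75 × 0.02) = 0.1225 SD, and power rises from 80% to Φ(0.3/0.1225 − 1.2816) = 88%.

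**The case against.** The strongest defense is that a condensed article may leave margins for secondary measures to the analysis plan, and that reporting an interval and letting clinicians weigh it is sensible estimation. The primary clinical conclusion also has its margin, alpha and decision rule. That last point stands in full: nothing here touches the responder analysis.

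The rest does not answer the concern. The article is not silent on the rule; it states one, judgment from the observed interval. A margin set in a later plan would replace that text rather than complete it. Nor does the article stop at estimation, since it says that non-inferiority will be evaluated.

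A reader might infer more than the text supports:
- **That CPOSS is to be tested with the responder procedures.** It is not; only the interval is named for CPOSS.
- **That the two procedures are confined to 2 × 2 tables.** The article does not say so. Its mention of such tables describes the stratified score method for adjusted % responders. What it shows is that procedures introduced for % responders are reused for means without explanation.
- **That most results could be called non-inferior.** Even a 0.5 SD margin fails observed deficits above about 0.30 to 0.32 SD.
- **That the plan ignores baseline.** A difference in mean change is valid under randomization. Additional Analyses plans a multivariable regression of end-of-study change and random regression models that include the baseline visit. Adjustment is a matter of efficiency, and it cannot help CPOSS, which is not measured at baseline.
- **That the stated ±0.3 SD can serve as the margin.** It is a precision for pre-to-post change, not a clinically acceptable loss.

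**Conclusion.** The point holds in this limited form. For CPOSS and for the mean changes in GDS, BDI, BAI and SF-36, the article states a decision rule that depends on the observed interval and has no margin, so the 10% one-sided error rate does not apply to those claims. CPOSS matters most because it is a named primary outcome.

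The size can only be illustrated. Between margins of 0.3 and 0.5 SD there is a band of results 0.20 SD wide whose classification is open, and against a true deficit of 0.3 SD the chance of a non-inferiority claim moves from 10% to 55%. These figures assume the margins shown, a normal approximation, and 100 per arm analyzed (the band is equally wide with 80). Fewer CPOSS scores at 12 months would lengthen the distance in step 2. The mismatch between test and outcome is narrower: it concerns the four clinical measures only and rests on the article's own wording.

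**What to change.** Before database lock, and without sight of results by arm, do one of the following for CPOSS and for each continuous score on which non-inferiority would be claimed:

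- Set a margin in points with a clinical rationale, and name which SF-36 score it applies to, since the instrument yields eight dimensions. State the power it gives; below about 0.33 to 0.37 SD the power falls short of the 85% used for the responder outcome, if unadjusted.
- Or label the analysis estimation only, and remove the sentence that leads from the interval to a judgment of non-inferiority.

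In Secondary Analyses, replace the two responder tests with a comparison of means shifted by the margin: ANCOVA with the baseline score as covariate for GDS, BDI, BAI and SF-36, and a plain difference in means for CPOSS. Compare the one-sided 90% limit with the margin.

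The cost is agreement on the margins and a change of wording; no new data are needed. The downside is that some results that could have been called non-inferior will no longer qualify.
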